**Objective:**

to deploy a web-based platform interoperating health surveillance systems from different hospitals to define models based on the highlighted risk factors to predict the occurrence of Latent Tuberculosis Infection (LTBI) and to define prevention strategies and interventions.

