**Methods:**

This is a cross-sectional ambispective observational study without drug and device. The primary endpoint is the prevalence of LTBI. The secondary endpoint is the identification of possible risk factors of LTBI in a large cohort of HCWs and students.

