## Materials and methods

### The aim

The Evolution of CROSSWORD Study is an ambispective observational study aimed at: 1) estimating the prevalence of LTBI in HCWs and students attending University Hospitals with focus on the association between LTBI and potential risk factors, and 2) creating a web-based platform interoperating health surveillance systems from different hospitals to define models based on the highlighted risk factors to predict the occurrence of LTBI and to define prevention strategies and interventions.

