## Procedures

### Primary outcome

The general objective of the research project is to develop an interoperable web-based platform to provide epidemiological and health surveillance against LTBI in the hospital setting. The primary outcome of the study is the prevalence of LTBI defined as 1) positive TST at enrollment, 2) tuberculin conversion defined as negative TST before enrollment and positive at enrollment, 3) subsequent positive QuantiFERON-TB Gold (QFT) test result performed on the same day as the positive TST result or within 5 days of tubulin conversion [higher response than the cut-off value of 0.35 IU/ ml of INF-γ was detected in at least one test tube (TB1 or TB2)], 4) chest imaging excluding pleural and/or pulmonary lesions suggestive of active tuberculosis and 5) final medical evaluation done by a Specialist in Infectious Diseases which excluded active disease. All five criteria must be met. One TST is scheduled for each participant. Furthermore, the study does not provide follow-up. Each participant continues regular annual follow-up as per routine clinical practice.

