## Statistical analysis

Descriptive statistics will be performed to characterize responses to the survey. The distribution of the qualitative variables will be shown in percentages, whereas the quantitative variable means, and standard deviations will be used after performing the Shapiro-Wilk test to verify their parametric distribution. Categorical variables will be compared using the Chi-squared test.

Logistic regression analysis will be performed to assess the association between LTBI and possible risk factors including age and sex, Bacillus Calmette–Guérin (BCG) vaccination history, previous work or stay in other countries with high TB rates, known recent (within 6 months) exposure to TB-infected patient, current smoking, co morbidities/ medical history, median QuantiFERON-TB Gold In-Tube level (TB Ag-Nil) if available, occupation, working/ training Unit and years working as HCWs.

The results of the risk-assessment analysis will be stratified according to sex, nationality, TB incidence of the country of birth and BCG vaccination and possible change in the roles of the participants and consequently in the risks of exposure.

Specific data visualization techniques will be used to provide a qualitative representation of the outcomes.

For the purposes of the project, cloud-based applications will be used to collect and store the data coming from the three healthcare centres. Data analytics will be adopted to measure the associations of risk factors with LTBI development. Finally, machine learning techniques will be used to predict the presence of LTBI with respect to health data and identified risk factors.

The final deliverable of the project will be a computerized decision support system able to deliver alerts in the case of LTBI presence.

*p-values* ≤ 0.05 will be considered statistically significant.

All the statistical analyses will be carried out using R statistical software (R Core Team, 2021).

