## Discussion

This study aims to enrich the primary prevention measures against TB, having a high socio-economic-health impact in high-risk populations (health-care workers and students) through an interoperable digital approach based on data obtained in three large Italian teaching hospitals (Fondazione Policlinico Universitario A. Gemelli IRCCS and Università Cattolica del Sacro Cuore, University of Palermo, and University Hospital of Bari).

The purpose of conducting LTBI prevention program for HCWs and students is to block the spread of TB by preventing infected persons from progressing to active TB. However, currently available diagnostic tests for LTBI have several limitations, such as variable specificity.

The enrolment of many HCWs and students through an ambispective clinical observation design will provide robust data on the prevalence of LTBI. Furthermore, the study will allow us to identify risk factors associated with the occurrence of LTBI. This data will make it possible to develop an interoperable digital platform integrating the health surveillance systems already in use with other data flows (medical record). Next, prediction models of LTBI, based on the identified risk factors, will be outlined. Finally, the accuracy of the prediction model will be evaluated through a validation phase which will include a new cohort of HCWs and students enrolled in the aforementioned teaching hospitals.

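### The outcome is a prevalence from one assessment, yet the aims and analysis speak of LTBI occurrence and development, and the case definition adds conversion over an unstated interval; one target should be fixed.

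*Protocol article*

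**What the plan says.** All references are to the protocol article.

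- **Design.** The abstract's Methods state: "This is a cross-sectional ambispective observational study without drug and device". Under Primary outcome, the outcome is named as prevalence, one TST is scheduled per participant, and "the study does not provide follow-up". Under Data management plans, the questionnaire is answered once.
- **Stated target: occurrence or development.** The abstract's Objective is "to predict the occurrence of Latent Tuberculosis Infection (LTBI) and to define prevention strategies and interventions", and The aim repeats it: "to define models based on the highlighted risk factors to predict the occurrence of LTBI and to define prevention strategies and interventions". The Discussion expects to "identify risk factors associated with the occurrence of LTBI". Statistical analysis says: "Data analytics will be adopted to measure the associations of risk factors with LTBI development".
- **Stated target: presence.** The next sentence of Statistical analysis says "machine learning techniques will be used to predict the presence of LTBI with respect to health data and identified risk factors", and the final deliverable is described as alerting to LTBI presence. The first part of The aim also speaks of prevalence.
- **Case definition.** Under Primary outcome, the second of five criteria is conversion: TST negative before enrolment and positive at enrolment. All five must be met. No interval for the earlier test is given.
- **Denominator.** Participants invites all HCWs and students. It excludes known tuberculosis, earlier chemoprophylaxis, a positive TST in the preceding 12 months and refusal of consent. It does not require an earlier negative TST.
- **Covariates.** Age, years working as HCW and known exposure within 6 months all enter the logistic regression. No time axis or exposure-time term is mentioned.

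**The concern.** A prevalence model and a model of new infection answer different questions, and the same coefficient supports different conclusions in each. Infection found at one screening visit is the sum of everything acquired up to that day. A factor that measures elapsed time can be associated with it even if it has no effect on the rate of acquiring infection. A factor that raises the rate briefly can show only a weak association.

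This matters because the protocol carries the identified risk factors into prediction models and prevention strategies. The end of the Introduction describes these as primary prevention strategies for LTBI, that is, preventing new infection. A prevalence analysis alone does not support that use.

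The conversion criterion adds a second ambiguity. Taken literally, a case is not any infection present at screening but a documented converter. The outcome is then called prevalence, defined as conversion over an unknown interval, and described in the analysis as development.

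**Working it through.** **1. The plan's own figure.** The sample size section uses n = Z²P(1−P)/d² with P = 0.01, d = 0.003 and 90% confidence.
- Z = 1.645: 1.645² × 0.0099 / 0.000009 = 2,976.6, so 2,977, as stated.
- Z = 1.64, as printed: 2,958.6, so 2,959.

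The figure reproduces. It is sized for a prevalence and implies about 30 cases (2,977 × 0.01 = 29.8).

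**2. If a case is any infection present at screening.** Assume a constant annual hazard h, the same for everyone, so that the true rate ratio for new infection is 1. The protocol gives no hazard; I use h = 0.05%, 0.1% and 0.2% per year. Prevalence after t years is 1 − exp(−ht), and the prevalence odds ratio for t₂ versus t₁ years is (exp(ht₂) − 1)/(exp(ht₁) − 1).

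| Contrast | When risk starts | h = 0.05% | 0.1% | 0.2% |
|---|---|---|---|---|
| 20 vs 5 years worked | at hire (no risk before) | 4.02 | 4.03 | 4.06 |
| Same people, age 45 vs 30 (hire at 25 assumed) | at birth | 1.51 | 1.51 | 1.52 |
| Years worked, given age | at birth | 1.0 | 1.0 | 1.0 |

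The value of h hardly matters; when risk is assumed to start matters a great deal. Where risk is lifelong, age carries the accumulated infection and years worked carries none once age is in the model.

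**3. The opposite distortion.** Assume h = 0.1% per year over 10 years, and a recent exposure that multiplies the hazard by five for six months. The cumulative hazard is 10 × 0.001 = 0.010 without exposure and 9.5 × 0.001 + 0.5 × 0.005 = 0.012 with it. The odds ratio is (exp(0.012) − 1)/(exp(0.010) − 1) = 1.20. A fivefold effect on the rate is barely visible in prevalence.

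**4. How much of a prevalence is recent.** If 1% prevalence built up at a constant hazard over 5 to 30 assumed years, the share of cases infected in the last year is about 20% (5 years), 10% (10 years), 5% (20 years) and 3% (30 years).

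**5. If conversion is required for every case.** The formula in step 2 still applies, with t now the time since the last negative TST.
- Equal intervals across participants: the artefact in step 2 largely disappears.
- Unequal intervals: at an equal hazard of 0.1%, 3 years versus 1 year gives (exp(0.003) − 1)/(exp(0.001) − 1) = 3.00. Any covariate correlated with the interval can pick this up.
- No earlier negative TST: the participant cannot be a case but stays in the denominator. If this is commoner among new entrants, short service would look protective by construction.

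**The case against.** The strongest reply is that the conversion criterion already gives the outcome an incidence component, so it is wrong to say that the design can model only infection present at screening. That stands. With annual visits, and a positive TST in the previous 12 months excluded, the intervals may be similar, and the distortion would then be small. But the protocol neither states the interval nor says that it will be accounted for, and it still calls the outcome a prevalence.

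It is also true that the machine-learning target and the deliverable are both stated as presence, that occurrence need not mean incidence, and that only development clearly does. The Discussion further gives the programme's purpose as stopping infected people from progressing to active disease. For that use, presence is the right target and accumulated exposure is a legitimate predictor. These points limit the concern to the statements about occurrence, development and primary prevention of LTBI.

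A reader might infer two stronger things. The first is that years of service would show a spurious tenfold effect: 20 versus 2 years counted from hire gives 10.05 to 10.18 for the hazards above. That figure sets the risk before hire to zero, which conflicts with an equal hazard for everyone. With lifelong risk and hire at 25, the contrast is age 45 versus 27 and the odds ratio is 1.67 to 1.70, or 1.0 for years worked given age. The tenfold figure should not be used. The second is that the investigators will take age or length of service as causes of new infection and direct prevention at long-serving staff. Nothing in the protocol says so; the wording permits that reading but does not announce it.

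**Conclusion.** The inconsistency is in the text. A prevalence outcome from one assessment is described in the aims and analysis as occurrence and development, elsewhere as presence, and is defined so that every case must be a converter since a test at an unspecified earlier time. Neither the prevalence nor the conversion reading, as written, yields clean rates of new infection.

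The size cannot be fixed from the document. Under an equal assumed hazard, the apparent effect of 20 versus 5 years worked ranges from none (lifelong risk, age in the model) to an odds ratio of about 4 (risk only from hire). Under the conversion reading it follows roughly the ratio of the intervals since the last negative TST, and is near 1 if those are equal.

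The point should be acted on because it is cheap to settle and changes what may be concluded. It does not affect the validity of a prevalence estimate or of a model for presence, provided the case definition matches that target.

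**What to change.** State one target and make the case definition under Primary outcome agree with it.

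If the target is LTBI present at screening:
- Replace occurrence and development with presence in the abstract's Objective, The aim, Statistical analysis and the Discussion.
- Report prevalence odds ratios and state that the model does not predict new infection.
- Do not require conversion for every case. Changing the words alone would leave a target that the case definition contradicts.
- Analyse conversion separately as an exploratory outcome, only among participants with a dated earlier negative TST, with the interval since that test accounted for (for example, log interval as an offset in a rate model).
- Base any claim about preventing new infection on that analysis alone.

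If conversion is to be the main target instead, restrict the denominator to participants with a documented earlier negative TST, account for the interval, and stop calling the outcome prevalence.

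The cost is wording, one additional analysis and a more modest claim. No extra testing is needed where dated records exist, but the protocol does not show that Palermo and Bari hold them, so the conversion analysis may be limited to some sites. It would also be small. Under the assumptions of step 4, and even if all 3,503 participants of the protocol's larger sample size had a dated test, a one-year interval would yield about 7 conversions (3,503 × 0.00201, 5-year build-up) down to about 1 (3,503 × 0.000335, 30-year build-up). It should be presented as descriptive.

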### Ethical considerations and declarations

The authors declare that the procedures will follow the ethical standards of the Declaration of Helsinki and the guidelines of good clinical practice. The Territorial Ethics Committee (CET) Lazio Area 3 has given its approval for the amendment prot. 3 of October 2^nd^, 2023 (ID: 3528, Prot. N. 0000627/23, December 11^th^, 2023), relating to the CROSSWORD Study (ID: 3528, Prot. N. 0046362/20, November 16^th^, 2020).

The authors confirm that all ongoing and related trials for this intervention are registered on ClinicalTrials.gov [NCT05756582].

The document informing participants about the study contains the reasons for completing the questionnaire and the potential benefits arising from analyzing the results. The participants will be informed that participation in the study is completely voluntary and that they can withdraw from the study at any time without negative consequences. The answers to the questionnaires will be treated confidentially and anonymously, and the handling of the data will also be confidential. The members of the Research Team will hand out the consent forms to the participants and will be available to answer any questions they may have about the study. The site PI and Co-PIs had access to information that could identify individual participants during or after data collection.

### The status and timeline of the study

The retrospective phase of the project started on November 17, 2021. The final data analysis will be completed by November 2024. The multicenter prospective phase started in September 2024. The estimated primary completion date is June 30, 2026. The estimated study completion date is December 15, 2026. The expected time for publication of results is the last quarter of 2026 (Fig 3).

**Fig 3 pone.0319568.g003:**
[figure not shown]
Chrono program of the Evolution of CROSSWORD Study. The Evolution of CROSSWORD study is an ambispective study including a retrospective phase focused on the analysis of data derived from the ongoing CROSSWORD Study, conducted at Fondazione Policlinico Universitario A. Gemelli IRCCS (FPG) and Università Cattolica del Sacro Cuore (UCSC) in Rome, and a prospective phase during which data will be collected from the University of Palermo (UNIPA) and the University of Bari (UNIBA)/ University Hospital of Bari, Italy.

## Discussion

This study aims to enrich the primary prevention measures against TB, having a high socio-economic-health impact in high-risk populations (health-care workers and students) through an interoperable digital approach based on data obtained in three large Italian teaching hospitals (Fondazione Policlinico Universitario A. Gemelli IRCCS and Università Cattolica del Sacro Cuore, University of Palermo, and University Hospital of Bari).

The purpose of conducting LTBI prevention program for HCWs and students is to block the spread of TB by preventing infected persons from progressing to active TB. However, currently available diagnostic tests for LTBI have several limitations, such as variable specificity.

The enrolment of many HCWs and students through an ambispective clinical observation design will provide robust data on the prevalence of LTBI. Furthermore, the study will allow us to identify risk factors associated with the occurrence of LTBI. This data will make it possible to develop an interoperable digital platform integrating the health surveillance systems already in use with other data flows (medical record). Next, prediction models of LTBI, based on the identified risk factors, will be outlined. Finally, the accuracy of the prediction model will be evaluated through a validation phase which will include a new cohort of HCWs and students enrolled in the aforementioned teaching hospitals.

After initiation of the trial, any changes to the protocol that impact the study objectives, study design, subject population, study procedures, or significant management aspects will require a formal protocol amendment. Any changes must be approved by Ethics Committees before implementation. Any deviation from the protocol must be documented and justified by a rationale and be subjected to approval. Any deviation from the protocol will be documented and justified by a rationale and will be subjected to approval. There will be no request for additional consent for the collection and use of data and biological materials from participants in ancillary studies. All complete confidential information relating to the study will be managed by the core Research Team (PI, Co-PI e site PI). Furthermore, the core Research Team will be responsible for the quality of data collection and their confidentiality. Only the team involved in the study will have access to the study documents which will be kept in a secure environment in accordance with ICH-GCP. Patient personal data, which is included in the investigator database, will be processed in accordance with all applicable laws and regulations. To protect patient identity, a unique patient identification code will be assigned to each patient/subject in the study and will be used in place of the patient/subject’s name when the investigator reports any study data. Therefore, this number, rather than the patient/subject’s name, will appear on all documents and will be referenced to the patient/subject’s date of birth.

The researchers intend to communicate the results of the trial to participants, healthcare professionals, and other relevant groups through scientific publications and national and international conference proceedings.
